4.6.2. Inclusion procedure

Possible patients for inclusion are:

- Patients who express their wish to participate in the study on the basis of the information they have received from their treating doctor or the nursing staff at the department of psychiatry.
- Patients who have been identified by medical or nursing staff at the department of psychiatry as being suitable for or interested in participating in the study.

These patients will receive written material and oral information about the project if they are interested. The oral information will elucidate the written information. They will also be informed that the treatment will not take place immediately, but at a time when beds are available in the ward in question. The patient will be included 1 week before the date at which a bed is available (see also trial phases). After inclusion, the patients will be asked not to disclose their type of treatment to the interviewer who assesses severity of depression by means of the Hamilton Depression Scale. This will be mentioned in the randomisation letter the patients receive at inclusion.

4.6.3. Inclusion criteria

- - Age between 18 and 70 years (inclusively).
  - Major depression according to DSM-IV diagnostic criteria (APA 1987).
  - Score of 13 or more on the 17-item Hamilton Depression Scale (Paykel 1990).

4.6.4. Exclusion criteria

- - Clinically dominant psychic or somatic anxiety corresponding to a score of 3 or more on items 10 and 11 (score range from 0 to 4) of the Hamilton Depression Scale (HAM-D17).
  - Clinically domonating suicidal ideation corresponding to a score of 3 or more (score range from 0 to 4) on item 3 of the Hamilton Depression Scale (HAM-D17), or if patient or investigator are not certain about the degree of suicidality.
  - Alcohol or drug abuse as defined in the M.I.N.I.
  - Epilepsy, as seizures can be triggered by sleep deprivation.
  - Unsafe contraception in women in the reproductive age. ½Safe contraceptive methods are: contraceptive pills, sterilisation, gestagen depot injections, subdermal hormone implantations, hormonal vaginal rings and transdermal depot patches. It is required that fertile women as a minimum use one of these methods over the total study period and two months after the end of the study.
  - Pregnant and lactating women. All women are pregnancy-tested by a urine sample test.
  - Psychotic disorder as defined in the M.I.N.I
  - Antisocial personality disorder as defined in SCID.
  - Borderline personality disorder as defined in SCID.
  - Schizotypal personality disorder as defined in SCID.
  - Clinically significant organic brain disorder or mental retardation causing incapacity.
  - Treatment with antipsychotics
  - Treatment with drugs with a well-known and significant interaction with duloxetine, e.g. isocarboxazide, thioridazine and fluoxetine. Patients in fluoxetine treatment may be included after one week's discontinuation of treatment.
  - Clinically significantly reduced kidney or liver function.
  - ECG abnormalities which may be of clinical significance in connection with the study or study medication.
  - High blood pressure not treated by medication
  - Glaucoma
  - Patients equally fulfilling the M.I.N.I. criteria for major depression and mania or hypomania and thus suffering from a mixed condition.
  - Patients who have a record that makes it doubtful that they can comply with the guidelines of the study (expected low compliance).
  - Patients who due to their medical history or physical tests during the screening procedure were found to have signs of a somatic condition requiring treatment.
  - Patients with bipolar disorder who have not been treated with a mood stabiliser for at least one month.
  - Allergy to filler components of duloxetine tablets.

4.6.5. Criteria for discontinuation of study treatment (end-points)

- The wish to discontinue treatment (sufficient follow-up treatment will be secured). In case of a waiting period treatment will be provided by the Psychiatric Research Unit.
- Patients with intolerable or clinically significant side effects.
- Patients who at any time during the first 9 weeks of the study have score of 15 or more on the Mania Scale (MAS) irrespective of a mania or hypomania diagnosis.
- Patients who display a continued clinical worsening of their depression at two subsequent weekly assessments (first nine weeks of the study).
  - Patients who after the primary hospitalisation experience a worsening of their depression and have to be re-admitted (first 9 weeks).
  - Mania requiring hospitalisation (first 9 weeks).
  - Change of mood stabilizer in bipolar patients (whole study).
  - Patients who do not comply with the single elements of the study will in general be discontinued (but see also "protocol deviations")

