4.1.1. Blinding procedures

It is not possible to blind the patient towards type of treatment (sleep deprivation or exercise). It is, however, possible to blind a permanent rater towards the treatment the patient has received. This can be done by having a rater who interviews and rates the patient each time throughout the whole study period by means of the Hamilton scale. The patients will be informed that they are not to disclose the type of treatment they receive to this permanent rater who assesses severity of depression according to Hamilton. There is no item in the Hamilton scale to reveal the type of treatment the patient receives, not even the sleep item, as all patients record their sleep in a sleep diary. The rater who conducts the interview will not meet the patient in the ward, as the regular visits are outside (before and after) the period of hospitalisation and will not be permitted to see patient records or CRFs. This rater will only receive the Hamilton rating sheet which does not contain information as to treatment group. All other procedures of the study will be performed by unblinded evaluators.

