4.6.6. Protocol deviations

The following protocol deviations do not mean exclusion from the study:

- - Skipping maximum one of three sleep deprivations in week 2.
  - Not taking up to 15% of the study drug duloxetine (first 9 weeks).
  - Not taking up to 15 % of other prescribed medication. (whole study period).
  - Skipping maximum 2 visits during the first 9 weeks and 2 visits during the following weeks until week 29.

When a patient discontinues participation in the study, this is recorded in the CRF together with the reason for drop-out and the type of follow-up. An individual assessment will decide whether to collect raw data from the last visit (exclusion visit) or from the last previous regular visit.

Collecting last visit data requires that the medicine prescribed has been taken according to the guidelines for compliance.

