**11. STATISTICS**

To analyse the number of patients with response or remission at three defined points in time (weeks 2, 9 and 29), Chi2 distribution is used. To do this, the Last Observation Carried Forward (LOCF) is employed. The assessment of the longitudinal courses of response and remission (and sustained response and remission) uses survival analysis (Kaplan-Meier survival-analysis) including log-rank test to calculate p values (Stassen et al 1993). Furthermore, the Mixed Model Repeated Measures (MMRM) (Brown et al. 1999) will analyse readily available depression scores to determine the difference between the two groups. Thus, MMRM does not use LOCF. The association between cortisol and depression scores and the association between urine and saliva cortisol has been calculated by means of the Spearman correlation coefficient *rho*. The same statistical method will be used to test the association between the various degrees of depression and the effect of sleep deprivation. The idiographic method will be analysed by means of MMRM. Exercise will be analysed as the percentage of compliance to the predefined goal (30 minutes exercise daily). Moreover, the achieved amount of exercise (combined score of the Borg scale and the amount of performed exercise) will be graded into light/moderate/intensive in follow-up phase I. It will be compared with the degree of response and remission in week 29 and analysed by Chi2 distribution. The number of study subjects has been calculated on the basis of an expected depression score of 24 on the 17-item Hamilton Depression Scale at inclusion into the study for both groups. After 9 weeks of treatment a decrease to 10 in group A and to 13 in group B is expected. The expected standard deviation is 4. With a type-I error of 0.05 and 0.90 power, 39 patients are required for each group.

No interim analyses have been planned.

GCP guidelines permit that patients may be excluded from the data analysis after the end of the study, if eligibility violations have taken place and if this was not known during the project. This may refer patients who have fulfilled the inclusion criteria, but have not taken any of the study medication, or have taken other prescriptions without telling the investigator, and where these violations were not known until the end of the study. All other patients assessed at the time of inclusion in the study are included in the statistical analyses according to the intention-to-treat method.

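### A patient removed for mania or re-admitted for worsening can be counted as a responder or remitter up to week 29, because the last HAM-D17 is carried forward and no later rating is provided for

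*Protocol*

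**What the plan says.** Section 4.6.5 is headed "Criteria for discontinuation of study treatment (end-points". Besides the mania score ("Patients who at any time during the first 9 weeks of the study have score of 15 or more on the Mania Scale (MAS"), it lists:

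- "Patients who after the primary hospitalisation experience a worsening of their depression and have to be re-admitted (first 9 weeks"
- admission to hospital because of mania, within the same period
- "Patients who display a continued clinical worsening of their depression at two subsequent weekly assessments (first nine weeks of the study"
- a change of mood stabiliser in bipolar patients, at any time in the study.

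Other sections treat such criteria as leaving the study, not only as stopping treatment. Section 4.2 says so for a MAS score of 15 or more, and section 4.5.5 for a change of mood stabiliser.

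When a patient leaves, section 4.6.6 has this recorded in the CRF "together with the reason for drop-out and the type of follow-up". The data kept come either from the exclusion visit or from the regular visit before it. The choice is made patient by patient, and exclusion-visit data may be used only if medication compliance was met.

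Section 11 compares the numbers with response or remission at weeks 2, 9 and 29 by chi-square test: "To do this, the Last Observation Carried Forward (LOCF) is employed". Section 4.3.1 defines response as a fall of more than half in HAM-D17 and remission as a score of 7 or less. No discontinuation reason overrides the score.

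**The concern.** Two of the events that end participation, mania and re-admission for worsening depression, are poor outcomes on any ordinary reading. Section 2.2 itself ties successful treatment to coming out of the depression and staying well for 6 months. Yet the primary counts look only at the last HAM-D17 used. If that score is low, the patient enters the week-9 and week-29 counts as a success although the plan removed the patient for a failure.

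The remedy depends on data collection. If the blinded rating stops when treatment stops, the true status at weeks 9 and 29 is lost for these patients, and no later analysis decision can recover it. The intention-to-treat claim in section 11 would then rest, for them, on a substituted value.

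**Working it through.** **1. Following the rules for two patients.**

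*Mania score.* MAS and HAM-D17 are rated at the same visits (Flowchart 1). Suppose that at week 3 a patient has MAS of 15 or more and HAM-D17 of 7 or less.
- Section 4.2: the patient leaves the study.
- Section 4.6.6: the closing score is 7 or less, from this visit or the one before if that was also low.
- Section 11: it is carried 9 − 3 = 6 weeks to week 9 and 29 − 3 = 26 weeks to week 29.
- Section 4.3.1: the patient counts as a remitter at both.

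*Re-admission.* Suppose a patient meets response at a weekly visit, then worsens and is re-admitted. The exclusion-visit score would probably be high and would protect the count. Section 4.6.6 lets the earlier score replace it in two ways: by the case-by-case choice, or because medication compliance was not met. The pre-relapse score then counts as response at weeks 9 and 29. All procedures except the Hamilton rating are done by unblinded staff (section 4.1.1), so this choice may be made with the allocation known.

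**2. Is there an override?** The only one is in section 4.3.2: extra sleep deprivation rules out early lasting remission, a secondary parameter. There is none for mania or re-admission.

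**3. The plan's own figure.** Inputs (section 11): week-9 means 10 and 13, SD 4, alpha 0.05 (two-sided assumed), power 0.90.
- Normal approximation: n = 2 × (1.960 + 1.282)² × 4² / 3² = 37.4, so 38 per group.
- Two-sample t-test: 38.35, so 39 per group, as stated. The sample size is not in dispute.

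**4. Rates implied by those inputs,** assuming normal scores and the expected baseline of 24:
- Remission (7 or less, cut at 7.5): A Φ((7.5 − 10)/4) = Φ(−0.625) = 27%; B Φ((7.5 − 13)/4) = Φ(−1.375) = 8%.
- Response (below 12): A Φ(0.5) = 69%; B Φ(−0.25) = 40%.

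**5. Effect of misclassification,** 50 per group (section 12). Each patient is worth 1/50 = 2 percentage points. The number misclassified is assumed, since the documents give no withdrawal rates. Chi-square without continuity correction, 100(ad − bc)² / (50 × 50 × successes × failures):

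| Week-9 count, A v B | Moved to failure | Chi-square | p |
|---|---|---|---|
| Remission 13 v 4 | none | 100 × 450² / (2500 × 17 × 83) = 5.74 | 0.017 |
| Remission 11 v 4 | 2 in A | 100 × 350² / (2500 × 15 × 85) = 3.84 | 0.050 |
| Remission 10 v 4 | 3 in A | 100 × 300² / (2500 × 14 × 86) = 2.99 | 0.084 |
| Remission 13 v 2 | 2 in B | 100 × 550² / (2500 × 15 × 85) = 9.49 | 0.002 |
| Response 35 v 20 | none | 100 × 750² / (2500 × 55 × 45) = 9.09 | 0.003 |
| Response 32 v 20 | 3 in A | 100 × 600² / (2500 × 52 × 48) = 5.77 | 0.016 |

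Two patients are enough to matter for remission, in either direction depending on the arm. Response is less sensitive.

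**The case against.** The case against has several parts, and much of it stands as a limit on the point.

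- **No sentence says that outcome ratings cease.** True. Removal from the study is explicit for MAS of 15 or more and for a change of mood stabiliser; for the other criteria it is the plain reading of section 4.6.6, which attaches no outcome visit to the follow-up it records.
- **A reader might infer that everyone who stops duloxetine is lost.** The documents do not support that. Section 4.5.1 keeps patients who switch antidepressant in the study, and the mania, worsening and re-admission criteria apply only in the first 9 weeks.
- **A reader might infer that a re-admitted patient cannot be rated,** because "The rater who conducts the interview will not meet the patient in the ward". In context that describes the planned hospital week, and section 4.1.4 allows visits on the ward when that stay is prolonged. The route to error is the choice of score in section 4.6.6.
- **Continued worsening would usually carry a poor score,** so it is not generally scored as success. Accepted.
- **A low HAM-D17 in a patient with a high MAS is an inference,** and the threshold applies without a diagnosis of mania. Accepted; the point is that nothing prevents such a patient being counted.
- **A reader might infer a bias towards Group A.** Section 2.2 puts the switch risk after sleep deprivation at the same magnitude as for antidepressants, and bipolar patients must have had a mood stabiliser for at least a month (section 4.6.4). The relapse it describes follows the next night's sleep, which here falls largely within the hospital week. The direction is unknown.
- **MMRM avoids LOCF, and an SAP could add a failure rule.** MMRM also lacks scores after removal and is not the primary count. An SAP could change the imputation but could not recover ratings never taken.

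**Conclusion.** The point holds in this form: followed as written, sections 4.2, 4.3.1, 4.6.5, 4.6.6 and 11 together can count a patient removed for mania, or re-admitted for worsening, as a responder or remitter up to week 29. For mania this needs only a low HAM-D17 at the closing visit. For re-admission it needs the earlier score to be used, which section 4.6.6 permits. The protocol also contradicts itself on whether these criteria end treatment or participation.

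The size is 2 percentage points per patient. The documents give neither the number of patients nor the direction between arms. The p-values are an illustration that assumes normal scores, the planning means and SD, and a chosen number of patients placed in one arm; they do not predict a false positive. The point is worth settling before enrolment, because ratings not collected are lost.

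**What to change.** Leave the clinical stopping criteria unchanged.

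1. Reconcile the heading of section 4.6.5, which speaks of stopping study treatment, with sections 4.2 and 4.5.5, which speak of leaving the study.
2. For patients who stop treatment and do not withdraw consent, continue the blinded HAM-D17 at the scheduled visits, at least weeks 2, 9 and 29. Use those scores in the intention-to-treat counts and in the MMRM.
3. Delete the case-by-case choice between exclusion-visit and earlier data in section 4.6.6.
4. Where no later rating exists after discontinuation for MAS of 15 or more, admission for mania, worsening or re-admission, count non-response and non-remission at later time points, and loss of sustained response in the Kaplan-Meier analysis. Worsening is included so that one rule covers all the failure criteria. Keep LOCF as a sensitivity analysis.

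The cost is protocol and consent wording, plus ratings by the existing rater at visits already in the schedule. The downside is that later scores will reflect whatever treatment followed, and response rates may be slightly lower.

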4.6.6. Protocol deviations

The following protocol deviations do not mean exclusion from the study:

- - Skipping maximum one of three sleep deprivations in week 2.
  - Not taking up to 15% of the study drug duloxetine (first 9 weeks).
  - Not taking up to 15 % of other prescribed medication. (whole study period).
  - Skipping maximum 2 visits during the first 9 weeks and 2 visits during the following weeks until week 29.

When a patient discontinues participation in the study, this is recorded in the CRF together with the reason for drop-out and the type of follow-up. An individual assessment will decide whether to collect raw data from the last visit (exclusion visit) or from the last previous regular visit.

Collecting last visit data requires that the medicine prescribed has been taken according to the guidelines for compliance.

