**4.3. Efficacy parameters**

4.3.1 The primary efficacy parameter is the number of patients in the two group that have achieved response to treatment or remission after 2, 9 or 29 weeks. Response is defined as a more than 50% reduction in HAM-D17 scores after inclusion into the study while remission is defined as a score of 7 or less on the HAM-D17.

4.3.2. Secondary effect parameter is the number of those patients in the two treatment groups who have experienced long-lasting response or remission after 9 weeks and after 29 weeks. Lasting response is defined as patients responding after 2 weeks of enrolment in the study and the response either lasting until week 9 (early lasting response) or until week 29 (episode response). Lasting remission is defined as being in remission after 2 weeks in the study and the remission either lasting until week 9 (early lasting remission) or until week 29 (episode remission). Response and remission are defined as mentioned under primary efficacy parameter. Patients who according to the protocol receive further sleep deprivations in week 4, 5, or 6 thus are cannot be defined as being in early, lasting remission. Response and emission are defined as mentioned under primary efficacy parameter. Patients who according to the protocol carry out additional sleep deprivation in weeks 4, 5 or 6 thus are defined not to be in early lasting remission.

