**4.4. Randomisation**

A computer-generated program for the randomisation codes was developed by the study statistician, [name], Department of Clinical Psychology, Odense University Hospital. The randomisation codes are in blocks. The number of patients per block is determined by the statistician and blinded towards the investigators. Each patient receives a numbered envelope prepared by the statistician and a secretary ([name]), containing a letter stating one of the two treatment groups. The envelopes are numbered and distributed consecutively, i.e. patient 1 gets the envelope with the number 1, patient 2 the envelope with number 2 etc. The patients, who after having received oral and written information have given their written informed consent to be included in the study, receive and open the envelope with information about the group they have been randomised to. The envelopes are kept in a locked closet at the Research Unit and are handed over to the investigator upon presentation of the signed informed consent statement on the day of inclusion. As the study is blinded towards the Hamilton rater, this rater will have no access to study patient records or study CRFs, in which the treatment group (A or B) is registered.

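### The rule for which visit supplies a drop-out's last score is discretionary, unblinded in practice and dependent on compliance, and it feeds the LOCF primary analysis

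*Protocol*

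**What the plan says.** Section 4.6.6 of the Protocol sets the rule for a patient who discontinues participation: "An individual assessment will decide whether to collect raw data from the last visit (exclusion visit) or from the last previous regular visit". The next sentence adds a condition: "Collecting last visit data requires that the medicine prescribed has been taken according to the guidelines for compliance". For duloxetine, the tolerance listed in the same section is up to 15% of doses missed, and it is stated for the first 9 weeks.

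On blinding, section 4.1.1 keeps the Hamilton rater blind and then states: "All other procedures of the study will be performed by unblinded evaluators". Section 4.4 adds that "this rater will have no access to study patient records or study CRFs, in which the treatment group (A or B) is registered".

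On the analysis, section 4.3.1 reads "The primary efficacy parameter is the number of patients in the two group that have achieved response to treatment or remission after 2, 9 or" (the sentence ends by naming week 29 as the third time point), with response and remission both defined on the HAM-D17. Section 11 states: "To analyse the number of patients with response or remission at three defined points in time (weeks 2, 9 and 29), Chi2 distribution is used". It applies LOCF to that test, adds an MMRM that does not use LOCF, and promises intention-to-treat analysis apart from violations that came to light only at the end of the study.

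Section 4.6.5 lists the reasons for stopping. They include further worsening over two successive weekly assessments in the first nine weeks, and non-compliance: "Patients who do not comply with the single elements of the study will in general be discontinued".

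**The concern.** Blind rating protects a score only if nobody who knows the allocation later decides whether that score counts. Under section 4.6.6 somebody chooses, patient by patient, between two visits. The section does not say on what ground, or that the choice must be made before the scores are known. Whichever visit is kept becomes the last observation, so the choice can decide whether a drop-out counts as a responder at a later time point.

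The compliance condition is a second problem. It removes a known exit score because of behaviour after randomisation. If patients stop their medication because of side effects or lack of effect, the score removed would tend to be the less favourable one. That sits badly with the intention-to-treat statement in section 11.

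At stake are the comparability of the two groups at weeks 9 and 29 and the type I error of the primary test. The MMRM is no full safeguard, because it too loses exit scores that are never collected.

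**Working it through.** **1. The plan's own figure.** Section 11 gives means of 10 and 13 at week 9, SD 4, alpha 0.05 and power 0.90. The normal approximation is n = 2(1.960 + 1.282)² × 4² / 3² = 37.4, so 38 per group. The two-sided t-test version gives 38.35, so 39, with power 0.905. The stated 39 per group is reproduced, and this point does not alter it.

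**2. Who makes the choice.** Section 4.6.6 does not say. Drop-out and its reason are recorded in the CRF (section 4.6.6), and medication taken is checked and recorded there (section 5). The blinded rater may see neither CRFs nor patient records (sections 4.1.1 and 4.4), and all other procedures are unblinded. The person applying the rule would therefore know the allocation. This is an inference from several sections, not a statement in the plan.

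**3. How the choice reaches the primary test.** The section 4.6.6 choice fixes the last score collected. LOCF (section 11) carries that score to the next analysis time point. The chi-square test then counts it as response or remission (section 4.3.1). With the expected baseline of 24, response means a HAM-D17 below 12.

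**4. Effect for one drop-out.** Suppose the two visits differ by 2 points. The change in the probability of response is P(X ≤ 13.5) − P(X ≤ 11.5), with X normal and SD 4:

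| Mean HAM-D17 | Change in response probability |
|---|---|
| 10 (planned, group A, week 9) | 16.3 points |
| 13 (planned, group B, week 9) | 19.6 points |
| 16 (assumed) | 13.6 points |
| 18 (assumed) | 7.8 points |
| 20 (assumed) | 3.5 points |
| 22 (assumed) | 1.2 points |

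The choice matters most near the cut-off and little for patients who are clearly still depressed.

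**5. Effect on the trial.** The simulation assumed no treatment difference, 50 per group (section 12), response as a score below 12, the uncorrected chi-square test and 20,000 runs per setting. Both visits had mean 12 and SD 4. Every drop-out in group A was given the better of the two scores and every drop-out in group B the worse. Drop-out rate and between-visit correlation are assumptions.

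| Drop-out | Correlation | False response difference | Type I error |
|---|---|---|---|
| 10% | 0.5 | 3.4 points | 7.1% |
| 10% | 0.7 | 2.6 points | 6.5% |
| 10% | 0.9 | 1.4 points | 5.9% |
| 20% | 0.5 | 6.6 points | 11.3% |
| 20% | 0.7 | 4.9 points | 8.4% |
| 20% | 0.9 | 2.9 points | 6.8% |
| 30% | 0.5 | 10.0 points | 18.2% |
| 30% | 0.7 | 7.6 points | 13.3% |
| 30% | 0.9 | 4.5 points | 8.0% |

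With a fixed rule (always the exit score), the mean difference was within about 0.1 point of zero in every setting. Type I error was 5.5% to 5.9%, on average about 5.7%.

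**The case against.** Several stronger readings are tempting, and the Protocol does not support them.

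- **That selection will happen.** The text allows it; nothing shows intent or occurrence. The compliance condition could even be read as the criterion for the individual assessment, which would make the choice less open. The text does not say so, and that criterion would itself depend on adherence.
- **That a non-compliant drop-out supplies no score.** Only the exit score is lost. The previous regular visit remains and the patient stays in the analysis. The intention-to-treat statement is weakened rather than plainly contradicted.
- **That the earlier score is always the better one.** A patient stopped after two successive worsening assessments may already have been worse at the previous visit.
- **That blind rating is the only protection against bias.** Allocation is randomised, with block size hidden from the investigators and numbered envelopes opened after consent (section 4.4). Blind rating is the safeguard against biased assessment specifically.
- **That a handful of choices decides the trial.** A change from 31/50 v 22/50 (p = 0.071) to 33/50 v 22/50 (p = 0.027) can be constructed, but it starts next to 0.05. At 16.3 to 19.6 points per drop-out, moving two patients takes about 2/0.196 = 10 to 2/0.163 = 12 drop-outs in one arm of 50, all decided the same way. Drop-outs further from the cut-off would need to be more numerous still.

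It could also be said that LOCF details belong in a statistical analysis plan. That would answer a silent protocol. This protocol already sets a rule, and the rule is discretionary and depends on compliance.

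**Conclusion.** The point stands as a badly fixed rule. Section 4.6.6 leaves a drop-out's last score to a choice without criterion, which the blinding arrangements place with staff who know the allocation. It also makes the exit score depend on adherence. LOCF brings the result into the primary analysis.

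The size cannot be fixed from the Protocol, which gives no drop-out rate, no between-visit correlation and no expected scores for drop-outs. The simulated type I error of about 6-7% at 10% drop-out, 7-11% at 20% and 8-18% at 30% is an upper illustration: every choice goes the same way and the scores centre on the cut-off. The true effect could be close to nil. Week 2 is probably least affected, because few patients will have left by then; weeks 9 and 29 are more exposed. The case for change rests on an avoidable opening for bias that is cheap to close, not on a demonstrated bias.

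**What to change.** Delete both sentences in section 4.6.6 and replace them with a fixed rule:

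- Every patient who stops has a HAM-D17 by the blinded rater at the exclusion visit, whatever the medication compliance.
- Where the patient agrees, the blinded HAM-D17 is still obtained at the scheduled weeks 2, 9 and 29 after treatment stops.
- An observed score at a time point takes precedence. If there is none, the value carried forward is always the latest available blinded HAM-D17 at or before that time point.

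This leaves nothing to decide case by case and removes the adherence condition. It keeps the exit scores for the MMRM and makes the data match the intention-to-treat statement in section 11. It changes no criterion for stopping treatment and not the 39 per group. The cost is a change of wording and a few additional ratings by the existing rater.
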